## Study Intervention

This study employs a sequential, multiple assignment, randomized trial (SMART) design to compare adaptive interventions for MCI. Participants will be randomly assigned to either control (receiving health education and routine care) or intervention groups receiving cognitive training with offline Taichi or virtual reality Taichi.

Non-responders at 12 weeks (defined as those unable to master the intervention content) will be re-randomized to alternative or intensified interventions. The study will incorporate stepping therapy up for those who continue to show cognitive decline with intensified interventions.

### Intervention Components

OffTC intervention will implement the standardized 24-form simplified Taichi exercise regimen, developed by the National Sports Administration in 1956 based on Yang-style Taichi principles. Modifications will be implemented for balance-intensive movements to enhance safety while maintaining form integrity.

VRTC intervention will utilize identical 24-form simplified Taichi movements implemented through an immersive technological interface. The VR system will incorporate precise arm-length calibration to accurately track upper and lower extremity movement trajectories.

Application: Guided Tai Chi (Developer: Cubicle Ninjas, Version 1.2.74, Release date: May 21, 2019)

Platform: Meta Quest VR Headsets.

[Video Supplementary files]

[figure not shown]

[figure not shown]
CT will utilize a comprehensive platform targeting multiple cognitive domains: memory, attention, executive function, logical reasoning, and reaction time. The system will be implemented via a customized WeChat mini-program interface.

[figure not shown]

## Procedures Involved

This study employs a prospective sequential, multiple assignment, randomized trial design. The 24-week SMART design comprises two 12-week phases. In the first phase, eligible participants will be randomly assigned to receive either offline Taichi plus cognitive training (OffTC+CT) or virtual reality Taichi plus cognitive training (VRTC+CT). Each intervention will consist of 1-hour weekly exercise combined with 1 hour weekly cognitive training.

At week 12, participants will be assessed for intervention mastery, with non-responders (defined as those subjectively unable to master the intervention content, scoring less than 3 on a 5-point Likert scale) being re-randomized to alternative or intensified interventions for the second 12-week phase. Responders in Group OffTC+CT will continue their original intervention protocol, while non-responders will be randomly assigned to either VRTC+CT or doubled doses of their original intervention (2OffTC+2CT). Similarly, responders in Group VRTC+CT will maintain their initial protocol, while non-responders will be randomly assigned to either OffTC+CT or doubled doses of their original intervention (2VRTC+2CT). The control group will receive only health education and routine care throughout the 24-week period.

The anticipated duration for individual participation in the study is 24 weeks (6 months). The duration anticipated to enroll all study participants is approximately 9 months (April to December 2023).

[figure not shown]

### Study Procedures

Registration to the study will occur after the subject consent is signed and eligibility is confirmed. Participants will be assigned to treatment groups using computer-generated randomization schemes, stratified by site. The first randomization will occur at baseline after the consent process is complete.

**First-Phase Intervention (Weeks 1-12)**

All participants assigned to intervention groups will receive either:

Offline Taichi plus cognitive training (OffTC+CT): 1-hour weekly OffTC sessions plus 1-hour weekly cognitive training

Virtual reality Taichi plus cognitive training (VRTC+CT): 1-hour weekly VRTC sessions plus 1-hour weekly cognitive training

The control group will receive health education and routine care.

**Assessment of Response (Week 12)**

At week 12, participants will be assessed for intervention mastery using a 5-point Likert scale. Those scoring less than 3 will be considered non-responders.

**Second-Phase Intervention (Weeks 13-24)**

Responders will continue their original intervention protocol. Non-responders will be re-randomized to either:

Alternative intervention: Switching from OffTC+CT to VRTC+CT or vice versa

Intensified intervention: Doubled doses of their original intervention (2OffTC+2CT or 2VRTC+2CT)

### Outcome Assessment

Participants' cognitive function will be monitored using the Memory Guard assessment tool at predetermined intervals (baseline, week 12, and week 24).

[figure not shown]

## Data and Specimen Banking

No specimens will be collected or banked for this study.

## Sharing of Results with Participants

This study does not involve diagnostic or genetic tests which could lead to the discovery of incidental findings that would need to be shared with the participant and/or the participant's medical team. The results of the cognitive assessments will be shared with participants at the conclusion of the study if requested.

## Study Population

### Inclusion Criteria

1. Age ≥60 years
2. MCI diagnosis established through positive screening on the Memory Guard assessment tool and confirmed by MoCA score <26
3. Demonstrated ability to complete assessments independently
4. Residence in the local community
5. Proficiency in smartphone operation

### Exclusion Criteria

1. Communication disorders
2. Severe impairment in activities of daily living
3. Presence of metal implants (e.g., cardiac pacemakers, artificial heart valves)
4. Severe psychiatric disorders
5. Illiteracy
6. Cognitive decline attributable to other pathologies (cerebrovascular disease, CNS infection, neurodegenerative disorders, traumatic brain injury, intracranial lesions, endocrinopathies, or vitamin deficiencies)
7. History of neurological diseases
8. Psychiatric disorders meeting DSM-5 criteria
9. Exercise contraindications
10. Color blindness
11. Insufficient education to complete testing protocols
12. Concurrent rehabilitation therapy
13. Regular exercise experience (e.g., Taichi, Baduanjin) within the preceding 3 months

### Screening

Potential participants will be screened using the Memory Guard assessment tool and the Montreal Cognitive Assessment (MoCA). Those with a positive screening on Memory Guard will be considered for inclusion. MoCA score <26 will be conducted to confirm eligibility based on the inclusion and exclusion criteria listed above.

## Vulnerable Populations

## Local Number of Participants

92 participants will be enrolled (approximately 30 each for OffTC+CT and VRTC+CT, and approximately 30 for control).

## Local Recruitment Methods

Community-dwelling older adults from three randomly selected districts in Shanghai will be systematically screened for MCI. Eligible individuals will be approached and provided with detailed information about the study.

Potential participants will be identified through community health centers, senior centers, and other venues serving older adults. Screening for MCI will be conducted using the Memory Guard assessment tool followed by the Montreal Cognitive Assessment (MoCA).

Participants will not receive financial compensation for participation, but all interventions will be provided at no cost.

## Withdrawal of Participants

Participants may withdraw from the study at any time without penalty. Investigators may withdraw participants if they develop conditions that meet exclusion criteria or if continued participation poses a risk to the participant's health or well-being.

Participants who elect to withdraw from the study will be asked to provide a reason for withdrawal, which will be documented. If possible, a final assessment will be conducted at the time of withdrawal.

## Risks to Participants

The potential risks associated with this study are minimal. Taichi exercise may cause mild muscle soreness or fatigue, particularly in participants who are not accustomed to regular physical activity. Virtual reality Taichi may cause mild dizziness or disorientation in some participants. These symptoms are typically temporary and resolve with rest.

The cognitive training component poses minimal risk but may cause mild frustration or fatigue in some participants. There is also a small risk of loss of confidentiality.

## Potential Benefits to Participants

Participants may benefit from improvements in cognitive function and physical health as a result of the interventions. Even if participants do not directly benefit, the knowledge gained from this study may help improve treatments for MCI in the future.

## Statistical Considerations

**Average Treatment Effects**

We will use causal forests double machine learning to estimate:

Total ATE between treatment and control groups on cognitive outcomes

Component-specific ATE for VRTC, OffTC, and CT

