## Secondary Aim

Evaluate the average treatment effects (ATE) of different intervention modalities (virtual reality Taichi, offline Taichi, and cognitive training) on cognitive scores measured by Memory Guard.

Analyze heterogeneity in treatment effects across participant subgroups based on cognitive status, comorbidities, and demographic characteristics.

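### Assigned cognitive-training hours always equal assigned Taichi hours, so randomisation identifies package effects but no stand-alone effect of VRTC, OffTC or CT

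*Protocol*

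**What the plan says.** Under Statistical Considerations, Average Treatment Effects, the protocol says "We will use causal forests double machine learning to estimate" two things: a total effect of treatment against control, and "Component-specific ATE for VRTC, OffTC, and CT". The Secondary Aim has the matching goal: "Evaluate the average treatment effects (ATE) of different intervention modalities (virtual reality Taichi, offline Taichi, and cognitive training", on the Memory Guard cognitive score.

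The dosing is set out in three places.

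- Procedures Involved: "Each intervention will consist of 1-hour weekly exercise combined with 1 hour weekly cognitive training".
- First-Phase Intervention: one active arm gets "1-hour weekly OffTC sessions plus 1-hour weekly cognitive training", the other "1-hour weekly VRTC sessions plus 1-hour weekly cognitive training". Control gets health education and routine care only.
- Second-Phase Intervention: "Responders will continue their original intervention protocol". Non-responders are re-randomised either to the other Taichi format, still with CT, or to the second option: "Intensified intervention: Doubled doses of their original intervention (2OffTC+2CT or 2VRTC+2CT".

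**The concern.** A component-specific effect needs some participants whose CT dose differs from their Taichi dose for reasons set by randomisation. The protocol describes none: no arm has CT alone, Taichi alone, or the two at different doses, and intensification doubles both together.

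At stake is a stated secondary aim. A causal forest will return a number for each component if it is asked to. Readers of a randomised trial would take those numbers as randomised evidence on what CT, VRTC or OffTC does by itself. The protocol itself argues, under Overcoming Limitations of Traditional Methodology, that evidence without randomisation is open to confounding.

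**Working it through.** The protocol gives no figure to reproduce here. The question is whether the planned effects are identified, so the check is on the assigned doses.

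**Inputs.** Two phases of 12 weeks (Procedures Involved). Phase 1: 1 h Taichi and 1 h CT per week in both active arms. Phase 2: responders unchanged; switchers change Taichi format and keep CT; intensified participants get 2 h and 2 h. The protocol does not restate the hours after a switch, so I take 1 h and 1 h from the phase 1 definition of that package.

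**Step 1: planned hours over 24 weeks.** Continuing gives 12×1 + 12×1 = 24 h of each component. Doubling gives 12×1 + 12×2 = 36 h. Switching gives 12 h of each Taichi format and 24 h of CT.

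| Path | VRTC | OffTC | CT | CT − (VRTC + OffTC) |
|---|---|---|---|---|
| Control | 0 | 0 | 0 | 0 |
| OffTC+CT, continue | 0 | 24 | 24 | 0 |
| OffTC+CT, switch | 12 | 12 | 24 | 0 |
| OffTC+CT, double | 0 | 36 | 36 | 0 |
| VRTC+CT, continue | 24 | 0 | 24 | 0 |
| VRTC+CT, switch | 12 | 12 | 24 | 0 |
| VRTC+CT, double | 36 | 0 | 36 | 0 |

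**Step 2: what this does to the component effects.** Write the mean outcome as a + v·VRTC + o·OffTC + c·CT. Substituting CT = VRTC + OffTC gives

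a + (v + c)·VRTC + (o + c)·OffTC.

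Only v + c and o + c appear. For any d, replacing (v, o, c) by (v − d, o − d, c + d) leaves the mean on every path unchanged. The data cannot choose between a large CT effect with no Taichi effect and the reverse.

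**Step 3: rank.**

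- Columns (VRTC, OffTC, CT): rank 2 of 3.
- With an intercept: 3 of 4.
- Phase 1 alone, with an intercept: 3 of 4.
- Hours entered separately by phase, with an intercept: 5 of 7, one column lost per phase.

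**Step 4: which contrasts are estimable** (is the contrast in the row space of the dose matrix?).

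- Not estimable: v, o, c.
- Estimable: v + c (VRTC+CT against control), o + c (OffTC+CT against control), v − o (VRTC against OffTC).

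Switching against doubling is also randomised, among non-responders within each first-stage arm. From OffTC it compares (12, 12, 24) with (0, 36, 36) hours, so it changes format and total dose together and isolates no component.

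**Step 5: does the chosen learner help?** Double machine learning works on the part of a treatment not predicted by the other variables. Assigned CT regressed on assigned VRTC and OffTC leaves a residual of zero. Dropping linearity does not help either: every assigned dose lies on the plane CT = VRTC + OffTC, and there are no data off it.

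**Step 6: ever/never coding.** Coding each component as ever or never received gives full rank, 4 of 4. This happens only because switchers then count as having both Taichi formats. It treats 12 h of a format like 24 h or 36 h, assumes additive effects, and draws the separation from a group selected for non-response. It does not give a randomised CT effect.

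**The case against.** **Minutes received may differ from minutes assigned.** CT is delivered through its own mini-program, separately from Taichi, and the protocol does not define the exposure for the component analysis. Received minutes could break the equality, so it would be too strong to say that no component estimate can be computed. This stands, but the variation is not randomised, and the estimate would be observational within a trial.

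**The seven paths may not be all of them.** Study Intervention also mentions stepping up for participants who keep declining and gives no doses. This stands as a limit on the count, which covers the paths the protocol specifies. That sentence describes a response to observed decline and mentions no randomisation, so it offers no randomised separation of components.

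**The analysis plan may settle it.** Details of the model can be left there. The source of the difficulty is the allocation, and no analysis plan can add doses that nobody was assigned.

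**Component may mean package.** CT is listed as its own item, yet it belongs to both packages. Read that way, its only contrast is all treatment against control, which the same section already lists separately.

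Three stronger readings are tempting and are not supported:

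- A reader might infer that doubled doses are confounded with poor mastery. That would affect a naive comparison of doubled with all other participants, which the protocol does not plan. Doubling is randomised among non-responders, and the planned method can adjust for covariates.
- A reader might infer that the component effects drive the recommended time allocations. The protocol describes causal discovery, a state space and reinforcement learning, and nowhere says that these effects enter that step.
- A reader might think that the Secondary Outcomes section has the same fault. It names average treatment effects without naming components.

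**Conclusion.** The point holds for the Secondary Aim and the Average Treatment Effects section. On every specified dosing path, CT hours equal total Taichi hours, so randomisation carries no information on any stand-alone component effect, at any sample size. It would be natural to read this as a problem with CT only. The algebra is symmetric: VRTC or OffTC against no Taichi is just as unidentified.

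The scope is one planned secondary analysis and the aim behind it. The total treatment-versus-control effect, each package against control and the comparison of Taichi formats are all identified. The conclusion rests on assigned hours as written and on switched packages keeping equal Taichi and CT hours. It needs no assumption about effect sizes, response rate or variance.

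**What to change.** In the Secondary Aim and in Average Treatment Effects, replace the component-specific effects with:

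1. OffTC+CT strategy against control;
2. VRTC+CT strategy against control;
3. VRTC+CT against OffTC+CT, as the comparison of Taichi formats;
4. switching against doubling among week-12 non-responders, within each first-stage arm.

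For item 3, name the time point. At week 12 both arms have been assigned 12 h of CT. By week 24 the average CT hours depend on how many participants in each arm were doubled, so the later contrast compares strategies.

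Add a sentence that this design cannot separate the effects of CT and Taichi. If a component estimate is kept, label it exploratory and model-dependent, define the exposure (for example, minutes received) and state the assumptions it needs.

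The cost is wording. No arm, dose, assessment or sample size changes; the sponsor gives up a claim that the randomisation does not support.

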**Heterogeneity in Treatment Effects**

We will analyze heterogeneity in treatment effects through:

SHAP value analysis to quantify the impact of participant characteristics on treatment effectiveness

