
### Added value of this study

This study represents the first exploration of adaptive optimal intervention strategies in MCI management through a causality-driven dynamic treatment regime framework by sequential, multiple assignment, randomized trial (cDTR-SMART). The cDTR-SMART is a generalizable computational framework for deriving adaptive optimal intervention strategies, which integrates Peter-Clark causal discovery algorithms to identify influential causal pathways and incorporates them into a state space model, ultimately utilizing reinforcement learning to determine optimal action spaces across different states.

In our analysis of participants, we identified cognitive status, age, and presence of diabetes and hypertension as key state space variables, which enabled the derivation of personalized optimal intervention combinations (Virtual reality Taichi, Offline Taichi, Cognitive function training) through our reinforcement learning model. The study revealed substantial individual heterogeneity in treatment responses, with an average treatment effect of 0·587 (95% CI [0·022, 1·152]). Notably, the intervention demonstrated pronounced effectiveness in older participants with lower cognitive states (ITE: 0.94), with this effect further amplified in the presence of chronic conditions (ITE: 1.12), suggesting that the most vulnerable subgroups might benefit most from the intervention. Additionally, SHAP analysis revealed that age demonstrated the most pronounced heterogeneous effects in VR Taichi responses, while diabetes status showed consistently positive clustering of SHAP values for offline Taichi practice, indicating enhanced benefits for participants with metabolic conditions. This data-driven approach transcends the generic non-pharmacological intervention guidelines in current dementia prevention protocols by providing actionable, precise intervention recommendations. Furthermore, by incorporating causal discovery methods, this approach offers interpretable insights into intervention intensity adjustments based on individual patient characteristics, making it both practically applicable and theoretically sound for personalized cognitive intervention.

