## Secondary Outcomes

Average treatment effects (ATE) of cognitive scores measured by Memory Guard.

Individual treatment effects (ITEs) across participant subgroups with different baseline characteristics.

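### SHAP value analysis is the only method the protocol names for its heterogeneity aim, and by itself it cannot support a claim of effect modification

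*Protocol*

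**What the plan says.** The Secondary Aim section sets the task: "Analyze heterogeneity in treatment effects across participant subgroups based on cognitive status, comorbidities, and demographic characteristics". The matching entry under Secondary Outcomes is "Individual treatment effects (ITEs) across participant subgroups with different baseline characteristics", with no measure of uncertainty attached.

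Under Statistical Considerations, the part on heterogeneity lists a single item: "SHAP value analysis to quantify the impact of participant characteristics on treatment effectiveness". The part on average effects begins "We will use causal forests double machine learning to estimate" and then lists only the total and the component-specific average effects. The causal forest is therefore not assigned to the heterogeneity aim.

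The section Added value of this study already reports results. It states "The study revealed substantial individual heterogeneity in treatment responses" and gives an "average treatment effect of 0·587 (95% CI [0·022, 1·152" (the upper confidence limit). It then reports "pronounced effectiveness in older participants with lower cognitive states (ITE: 0.94" and a larger value, 1.12, for the same kind of participant with chronic conditions. Neither subgroup figure has an interval or a subgroup size. SHAP patterns for age and diabetes are described after these figures as further findings.

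**The concern.** A SHAP value splits a model's prediction among its inputs. It answers how the fitted model uses a covariate, not whether the treatment effect truly differs by that covariate. If a flexible model has fitted noise, SHAP attributes that noise to covariates just as readily as it would attribute signal. It supplies no standard error, interaction test or check that the predicted differences hold up out of sample. Naming it as the method for a stated aim is a choice of method, not a detail left for later.

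At stake is the suggestion that the most vulnerable participants might benefit most, and the claim of substantial individual heterogeneity. An analysis carried out as this section is worded would offer no way to tell such a pattern from chance.

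**Working it through.** **Inputs.** From Added value of this study: average effect 0.587, 95% CI 0.022 to 1.152; subgroup effects 0.94 and 1.12. From Local Number of Participants: 92 enrolled, about 30 per arm. The subgroup share f is not given, so it is an assumption, varied from 10% to 50%.

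**Step 1: the reported average effect.** The interval midpoint is (0.022 + 1.152)/2 = 0.587, which matches the stated estimate. The standard error is (1.152 − 0.022)/(2 × 1.96) = 0.288, so z = 0.587/0.288 = 2.04 and two-sided p = 0.042. This checks internal consistency only.

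**Step 2: distance of the subgroup figures from the average.** 0.94 − 0.587 = 0.353, or 1.22 standard errors of the average effect. 1.12 − 0.587 = 0.533, or 1.85 standard errors. Neither allows yet for the larger error of a subgroup estimate.

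**Step 3: subgroup against the rest.** Assume the same residual SD and allocation ratio in every subgroup. The subgroup SE is then 0.288/√f, and the contrast with the remaining participants has z = [(subgroup effect − 0.587)/0.288] × √(f/(1 − f)).

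| Share f | Subgroup SE | 0.94: 95% CI | z, p | 1.12: 95% CI | z, p |
|---|---|---|---|---|---|
| 10% | 0.912 | −0.85 to 2.73 | 0.41, 0.68 | −0.67 to 2.91 | 0.62, 0.54 |
| 25% | 0.577 | −0.19 to 2.07 | 0.71, 0.48 | −0.01 to 2.25 | 1.07, 0.29 |
| 50% | 0.408 | 0.14 to 1.74 | 1.22, 0.22 | 0.32 to 1.92 | 1.85, 0.06 |

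Every interval contains 0.587. Setting z = 1.96 and solving for f, p<0.05 would need a share above about 72% for 0.94 and about 53% for 1.12.

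**Step 4: the amplification from 0.94 to 1.12.** As worded, the second group appears to be nested in the first. If the first is 50% of the sample (SE 0.408) and half of it has chronic conditions (both assumed), the SE of the nested difference is 0.408 × √(1/0.5 − 1) = 0.408. Then z = (1.12 − 0.94)/0.408 = 0.44 and p is about 0.66.

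**Step 5: what this precision could detect.** With 80% power and two-sided 5%, the detectable difference between two subgroups is (1.96 + 0.84) × 0.288 × √(1/f + 1/(1 − f)). That is about 1.62 for a 50/50 split and 1.87 for a 25/75 split, or 2.8 and 3.2 times the average effect.

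**The case against.** The strongest reply is that the protocol does not rest heterogeneity on SHAP alone. Subgroup effects are a separate secondary outcome, the families of modifiers are named, and a causal forest can produce conditional effects. The 0.94 and 1.12 figures are themselves effect estimates reported beside the SHAP findings, not SHAP output. This stands in part: those two figures should not be presented as products of SHAP. But the text assigns the forest to average effects and attaches no inference to the subgroup outcome, so SHAP remains the only method it names for this aim.

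Intervals, tests and multiplicity rules are often left to the SAP, which is not at hand. A reader might infer that nothing in the eventual analysis could refute a heterogeneity claim. The protocol cannot show that. The point is narrower: the method it does name is unsuitable for the aim.

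A reader might also infer that SHAP drives the personalised recommendations. The documents do not support this. The Primary Outcome section and Added value of this study both derive the strategy by reinforcement learning, and no text feeds SHAP output into it. The statement about vulnerable subgroups is also hedged.

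On the numbers, both subgroup figures lie inside the average effect's confidence interval, and it is tempting to treat that as decisive. It is not a test of heterogeneity, because that interval describes uncertainty in a mean. The subgroup-versus-rest contrast is the relevant check, and it depends on an assumed share and on the 1/√f scaling. A forest that borrows strength across participants could have smaller errors; choosing subgroups after seeing the data works the other way.

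**Conclusion.** The point holds in this form: the protocol fixes, for a stated secondary aim, a method that cannot by itself support a claim of effect modification, and it attaches no inference to the subgroup effects. Under the assumptions above, the reported subgroup figures are compatible with a constant effect at every share from 10% to 50%, with p no smaller than 0.22 for 0.94 and 0.06 for 1.12. The 50% share is generous for 1.12, since that group appears to be a subset of the other.

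A reader might go further and conclude that the effect is homogeneous. The figures do not show that. With a detectable difference near three times the average effect, the trial could miss large heterogeneity. What is missing is support for the claim. The correction should be made, but it concerns a secondary aim and does not touch how the primary strategy is derived.

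**What to change.** In the heterogeneity part of Statistical Considerations:

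- Use the planned causal forest to report cross-fitted group average effects and between-group differences, with 95% confidence intervals. Do so for a short fixed list of modifiers drawn from the Secondary Aim (cognitive status, comorbidities, demographics), with cutpoints set, since the aim gives none.
- Add one omnibus calibration or best-linear-predictor test on out-of-fold predictions, and make it the gate for any claim of heterogeneity.
- Adjust the between-group contrasts for multiplicity. Allowing a claim on any one of, say, an omnibus test and four contrasts, assumed independent at 5%, would give 1 − 0.95^5 = 23% false claims.
- Label the analysis exploratory. Results already appear in the protocol, so a change made now cannot be called prespecified.
- Keep SHAP as a descriptive plot, and call the quantities under Secondary Outcomes conditional (group) average effects, since 0.94 and 1.12 are given for described groups and not for individuals.

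The cost is a little extra analysis on a model already planned, with no new data. At this precision the gate will often not be passed, and the heterogeneity claims will probably weaken.
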